### Analyses and statistical power

We aim to recruit 20 children to each arm of the trial. Recruitment will stop once the target number of participants is recruited and within two years from the beginning of the study. No interim analyses will be performed before all data is collected. Definitive comparisons of the interventions will not be undertaken due to the feasibility nature of the study. Details of patient screening, recruitment, retention, withdrawal, and follow-up will be summarized (see research questions above). Adherence to U-VBF will be measured according to the number of patients who complete the intervention in accordance with the treatment manual. Adherence to treatment dosage will be recorded using an intervention pro-forma in each session where the SLT records a tick mark for each trial (i.e., each time the patient attempts to produce the speech sound in treatment, this should be around 100 for both interventions). All sessions will be audio-recorded (consent permitting) and 20% of sessions will be fidelity checked for dosage and adherence to protocol by the research SLT, blinded to group allocation.

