## Methods

A single-center mixed-methods two-arm parallel group pilot randomized controlled trial with blinded assessors will be carried out. Cases will be stratified by three age groups (4;6–7;11; 8;0–11;11 and 12;0–16;0). A wide age-range was chosen for pragmatic reasons. That is, to both aid recruitment and reflect the typical age range treated with both types of intervention. This will also allow us to gather information about the feasibility of the treatment across different ages and use this information to inform the eligibility criteria of the large-scale study. Due to the nature of the U-VBF, therapists and patients will not be blinded to treatment allocation but the limitations of this will be mitigated by the use of an assessor, blinded to group, and evaluators, blinded to both group and treatment time point. Unblinding to the assessor or the evaluator will not be permissible and is considered unnecessary given the clinicians delivering the intervention are not blind to treatment allocation.

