### Outcome measures

A blinded assessor will collect measures at baseline (-t1: pre-treatment), 2 months post-randomization (t7, to allow for any delays in referral to therapy), and 3 months post-randomization (t8) to see if any benefit is maintained. Assessment will take place in a university clinic or via video-conferencing and will be carried out by a research SLT blinded to group for primary outcome measures and by the treating SLTs for within-session measures (Table 1).

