### Ultrasound/speech analysis

All of the speech measures at baseline, and follow-up will be recorded with simultaneous ultrasound in both groups by a research SLT blinded to group where possible. Our previous work showed that the addition of ultrasound to transcription increases inter-rater reliability and allows identification of covert (imperceptible to the ear alone) errors [9]. This will allow us both to calculate PTC (the primary outcome measure) with increased reliability and to perform an error analysis. Twenty-five percent of the data will also be rated by two specialist cleft SLTs (not involved in the project) trained in ultrasound-aided transcription. These SLTs will also rate the audio recordings from the within-treatment sessions (t1 to t6 in Table 1), blinded to group.

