### Roles and Responsibilities

#### Principal Investigator ([name])

- Design and conduct of Sonospeech
- Preparation of protocol and revisions
- Preparation of participant information sheets and consent forms
- Organizing steering committee meetings
- Publication of study reports

Steering Committee

- See title page for all members
- Agreement of final protocol
- All lead investigators will be steering committee members
- Recruitment of patients and liaising with principle investigator
- Reviewing progress of study and if necessary agreeing changes to the protocol or personnel

Trail Management Committee

- Principle Investigator and Research Speech and Language Therapist
- Study planning
- Organization of steering committee meetings
- Ethical applications
- Provide annual report to ethics committee
- Reporting of serious adverse events
- Budget administration and contractual issues
- Data checking and verification
- Randomization, in collaboration with the clinical trials unit

Data Manager

- Research Speech and language therapist
- Maintenance of data entry and data storage

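### The therapy-session fidelity check cannot be done blind to arm, and as written it leaves the outcome assessor's blinding unprotected before t7 and t8

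*Protocol article*

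**What the plan says.** Methods accepts that therapists and families know the allocation. It says the resulting limitations are "mitigated by the use of an assessor, blinded to group, and evaluators, blinded to both group and treatment time point", and adds: "Unblinding to the assessor or the evaluator will not be permissible".

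Outcome measures says that assessment at baseline, t7 and t8 is "carried out by a research SLT blinded to group for primary outcome measures". Ultrasound/speech analysis says the baseline and follow-up speech measures are "recorded with simultaneous ultrasound in both groups by a research SLT blinded to group where possible".

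Analyses and statistical power covers the treatment sessions. It begins "All sessions will be audio-recorded (consent permitting", and then says that "20% of sessions will be fidelity checked for dosage and adherence to protocol by the research SLT, blinded to group allocation". The same section measures adherence to U-VBF against that intervention's treatment manual.

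Appendix 2 gives the membership of the trial management committee as "Principle Investigator and Research Speech and Language Therapist". Its tasks include "Randomization, in collaboration with the clinical trials unit". The research SLT is also listed as data manager, responsible for data entry and storage. No second research SLT role appears there.

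**The concern.** One role is asked to do two things that do not fit together. It must stay blind to arm in order to collect the primary outcomes, and it must judge whether recorded therapy sessions followed the protocol for their arm. The second task discloses the arm.

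PTC depends on a human judgement of correct or incorrect production, and it includes stimulability, where the way the assessor elicits the sound may matter as well as how it is scored. The Discussion concedes that treating clinicians may prefer the novel intervention. An assessor who knows the arm could tilt elicitation or scoring in the same direction.

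The Background says a full-scale RCT of similar design follows if the criteria are met. A blinding arrangement that was not secure in the pilot could therefore be carried into the definitive trial as though it had been shown to work.

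**Working it through.** The plan gives no figure on this point, so there is none to reproduce. The check compares the role assignments and then illustrates the possible exposure.

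**1. Can the fidelity check be blind?** It has two parts.
- Dosage: counting attempts at the target sound could perhaps be done without attending to the arm.
- Adherence: the standard differs by arm. U-VBF has its own manual, and the SLT guides the child from a live tongue image with recording and playback. Articulation intervention uses modelling, demonstration and verbal description. A checker must know which standard applies, and talk about the tongue image would be expected on the U-VBF recordings. Blinding to group is therefore not achievable for this part.

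**2. Would removing names help?** Probably not. Data management itself acknowledges that voice recordings can identify participants, and the checker belongs to the role that assesses these children in person or by video.

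**3. Is the checker the outcome assessor?** Outcome measures and Ultrasound/speech analysis refer to a research SLT; Analyses and statistical power refers to the research SLT. Appendix 2 lists one such role. The text does not say that one person does everything, but it provides no second role.

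**4. Does timing protect the assessor?** Within-treatment session outcomes defers rating of the session wordlists to the end of the project. Analyses and statistical power puts no such condition on the fidelity checks, so they may precede t7 and t8.

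**5. How many children could be affected?**
- Inputs: 20 children per arm, so 40 in all; six sessions each; 20% of sessions checked.
- Planned sessions: 40 × 6 = 240. Checked: 0.20 × 240 = 48.
- Fewest children, if all six sessions of the same children are checked: 48 / 6 = 8.
- Most children, if checks are spread out: all 40, since 48 exceeds 40.
- Under simple random sampling of sessions (an assumption; the plan gives no scheme), P(a child has at least one checked session) = 1 − C(234,48)/C(240,48) = 0.742, and 0.742 × 40 = 29.7, about 30 children. Independent sampling of sessions gives nearly the same: 1 − 0.8⁶ = 0.738.

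These figures count children with any checked session. They do not count children whose arm is known to the assessor before t8, because that depends on when the checks are done. Refused consent to recording would lower them.

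**The case against.** **Blinding might survive in practice.** The checks could all be done after t8, or by a different research SLT, and outcome collection would then be intact. This stands as a reason not to say that assessor blinding must fail. It does not rescue the text, which fixes neither arrangement and calls the check itself blinded.

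**Scoring has other safeguards.** Methods separates the assessor from evaluators who are also blinded to time point. Two outside SLTs rate 25% of the data and also the within-session recordings, blinded to group. This stands for part of the data: exposure of the person collecting outcomes is not exposure of every rater. But the outside SLTs rate that 25% in addition to a main rater whom the text does not clearly identify, and blinded scoring cannot undo a difference in how responses were elicited.

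**The wording on blinding is qualified.** Ultrasound/speech analysis says where possible. If that qualifies the blinding, it conflicts with the absolute rule in Methods.

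**A reader might infer more from Appendix 2**, namely that the research SLT learns every child's arm through the randomization and data-manager tasks. The documents do not support that. Randomization says the trials unit randomizes, and the committee's share could be handled by the principal investigator alone. Nothing shows that the data manager sees allocations or session forms before t8, and an article commonly leaves access rules to the full protocol. What remains is a request for one clarifying statement.

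**No feasibility result depends on it.** This is correct. The criteria concern recruitment, retention, completion, acceptability and dosage; none uses PTC by arm, and definitive comparisons are excluded.

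**Conclusion.** The point holds in a limited form. Blinding to group cannot be achieved for a check of adherence to an arm-specific intervention. Because the plan gives that check to the role that collects the blinded primary outcomes, and does not defer it, the assessor blinding relied on in Methods is not protected before t7 and t8.

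The size is 48 checked sessions from 8 to 40 children. The figure of about 30 rests on random sampling, and the number unblinded before t8 cannot be derived from the text. The conclusion assumes that the single research SLT role in Appendix 2 is also the outcome assessor, and that Table 1, which is not shown in the text read here, does not schedule the checks after t8.

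It does not follow that blinding fails for all children or that the pilot's go/no-go decision is affected. The consequence is possible bias in the candidate PTC data and an insecure arrangement passed to the full trial. This should be fixed, but it does not undermine the pilot's stated objectives.

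**What to change.** 1. In Analyses and statistical power, either hold all fidelity checks until t8 assessment and PTC scoring are locked, or assign them to an existing role that neither collects nor scores outcomes. Delete the statement that this task is blinded to allocation.
2. In Appendix 2, state that the research SLT acting as outcome assessor neither receives allocations nor handles treatment-session data before that lock.

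The cost is a re-ordering or reassignment of tasks among existing staff and two changes of wording. If the checks are deferred, feedback on fidelity comes too late to correct delivery during the trial. If they are reassigned, that feedback stays timely but another role must find the time for 48 sessions.

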### Ultrasound/speech analysis

All of the speech measures at baseline, and follow-up will be recorded with simultaneous ultrasound in both groups by a research SLT blinded to group where possible. Our previous work showed that the addition of ultrasound to transcription increases inter-rater reliability and allows identification of covert (imperceptible to the ear alone) errors [9]. This will allow us both to calculate PTC (the primary outcome measure) with increased reliability and to perform an error analysis. Twenty-five percent of the data will also be rated by two specialist cleft SLTs (not involved in the project) trained in ultrasound-aided transcription. These SLTs will also rate the audio recordings from the within-treatment sessions (t1 to t6 in Table 1), blinded to group.

### Data management

All data will be stored in a dedicated secure shared drive managed by the University of Strathclyde where it will be automatically backed up. Hard copies of data will be kept at the hospital and the University of Strathclyde. Participants will be pseudo-anonymized during the project, with a key linking codes to actual names held securely at the university. The key will be deleted at the end of the project and data will become anonymous. Participants and their families will be informed that recordings of voice can be identifiable.

### Harms

Based on previous studies using ultrasound intervention for speech sound disorders, no harm to the participants is anticipated. In rare cases, some people may have an allergic reaction (contact dermatitis) to the gel [24]. If this is observed, the gel can be substituted with water. If water does not achieve a sufficiently good ultrasound image, then the participant may be discontinued from the trial. If any adverse consequences are observed, they will be recorded in the participant’s clinical notes and reported to the NHS ethics committee using standard procedures. The ethics committee and the university ethics committee can audit the trial at any time. The study has been granted ethics approval by the West Midlands-South Birmingham Research Ethics Committee, reference number 21/WM/0104.

### Dissemination policy

The results from this study will be published in academic journals, such as The Cleft Palate Craniofacial Journal, Clinical Linguistics and Phonetics. Additionally, results will be presented at academic and clinical conferences such as the International Congress of Cleft, Lip and Palate and Related Craniofacial Anomalies, and the conference of the Royal College of Speech and Language Therapists, where it will reach both an international and a local audience of clinicians.

The protocol, statistical code and the anonymized final numerical dataset will be made available publicly on the University of Strathclyde’s open access repository “PURE”. Protocol changes will be reported to the trial registry and the ethics committee.

## Discussion and summary

This pilot feasibility study will determine whether a full-scale randomized control trial comparing ultrasound visual biofeedback to treatment as usual (articulation intervention) for the treatment of cleft speech characteristics is feasible. Prior studies such as [21] suggest that children with CLP can tolerate ultrasound recordings and studies such as [14] suggest good retention in ultrasound intervention, with only one child in this study lost to follow-up. We therefore predict that the objectives outlined above will be met, and if this is the case a full-scale, adequately powered, multi-center RCT will be warranted. Within this planned larger RCT, we hypothesize that U-VBF will show quicker acquisition of speech sounds in error, leading to shorter time in intervention, reduced frustration for patients, and cost savings. Nevertheless, there are some potential limitations to the current study. Firstly, it is not known how acceptable randomization will be to patients and carers, and it is possible that carers will express a preference for the trial intervention, given the novelty of the technology used in U-VBF [23]. To mitigate this, patients will be offered U-VBF at the completion of the study, if their speech errors remain. A previous study trialing a similar technology-based intervention with children with Down syndrome showed that no children were lost to follow-up in either arm of the trial when this was offered [32]. A further limitation of the current study, which cannot be completely mitigated, is a potential preference from the treating clinicians for one intervention over the other, in particular the trial intervention. This could lead to increased outcomes in the trial intervention, which are not due to the visual biofeedback per se, but more to increased motivation in the intervention sessions [33]. Finally, a recent move towards more use of telehealth due to the COVID-19 pandemic, means that U-VBF is disadvantaged compared to articulation intervention, because it is a behavioral intervention which requires hardware and therefore only be can only be carried out in person, rather than over video-conferencing. It therefore currently may be more difficult to recruit to a trial which involves travel to a hospital or university.

In conclusion, this feasibility study will determine whether a larger trial comparing U-VBF and Articulation Intervention is both feasible and acceptable to patients and their carers. Notwithstanding the limitations, we predict that achieving the success objectives related to recruitment, retention, and acceptability outlined above will motivate a full scale RCT which in turn seeks to determine whether U-VBF shows improved outcomes over treatment as usual for speech disorders associated with cleft lip and palate.

## Data Availability

All data underpinning this publication are openly available from the University of Strathclyde PURE Knowledge Base at: 10.15129/f65343c4-7781-44fe-9b00-516d4597efac.

## Appendix 1

Table 2

**Table 2 Tab2:** WHO trial items

Data category	Information
Primary registry and trial identifying number	ISRCTN 17441953
Date of registration in primary registry	22 March 2021
Secondary identifying numbers	
Source(s) of monetary or material support	Chief Scientist Office of Scotland
Primary sponsor	University of Strathclyde
Secondary sponsor(s)	N/A
Contact for public queries	[contact]
Contact for scientific queries	[contact]
Public title	Ultrasound visual biofeedback versus standard treatment for children with cleft lip and palate
Scientific title	SonoSpeech Cleft Pilot: a pilot randomized control trial of ultrasound visual biofeedback versus standard intervention for children with cleft lip and palate
Countries of recruitment	Scotland
Health condition(s) or problem(s) studied	Cleft lip and palate
Intervention(s)	Active comparator: ultrasound visual biofeedback
	Treatment as usual: articulation intervention
Key inclusion and exclusion criteria	Ages eligible for study: 4 to 16 years
	Sexes eligible for study: all
	Accepts healthy volunteers: no
	Inclusion criteria: speech disorders associated with cleft lip and palate
	Exclusion criteria: no spoken English; severe hearing loss; severe learning disability
Study type	Interventional
	Allocation: randomized intervention model. Parallel assignment masking: single blind (investigator, outcomes assessor)
	Primary purpose: treatment
	Phase II
Date of first enrolment	October 2021
Target sample size	40
Recruitment status	Recruiting
Primary outcome(s)	Percentage targeted consonants correct measured using speech assessment as the percentage of treated speech sounds produced correctly in words at baseline, 6 weeks, and 3 months
Key secondary outcomes	1. Patient- and carer-reported speech function and intelligibility for children aged ≥ 8 years measured using the Intelligibility in Context Scale and the CLEFT-Q speech function scale at baseline, 6 weeks, and 3 months 2. Patient- and carer-reported quality of life for children aged ≥ 8 years measured using the CLEFT-Q quality of life scale at baseline, 6 weeks, and 3 months 3. Patient and carer satisfaction with both interventions measured using the Experience of Service Questionnaire at 6 weeks, and 3 months

## Appendix 2

### Roles and Responsibilities

#### Principal Investigator ([name])

- Design and conduct of Sonospeech
- Preparation of protocol and revisions
- Preparation of participant information sheets and consent forms
- Organizing steering committee meetings
- Publication of study reports

Steering Committee

- See title page for all members
- Agreement of final protocol
- All lead investigators will be steering committee members
- Recruitment of patients and liaising with principle investigator
- Reviewing progress of study and if necessary agreeing changes to the protocol or personnel

Trail Management Committee

- Principle Investigator and Research Speech and Language Therapist
- Study planning
- Organization of steering committee meetings
- Ethical applications
- Provide annual report to ethics committee
- Reporting of serious adverse events
- Budget administration and contractual issues
- Data checking and verification
- Randomization, in collaboration with the clinical trials unit

Data Manager

- Research Speech and language therapist
- Maintenance of data entry and data storage
